## **Synopsis of the Clinical Trial Protocol**

The AIDS vaccine (Nucleic Acid in Combination with Recombinant Vaccinia Tiantan) has been jointly developed by the Center for Disease Control and Prevention of Sexually Transmitted Diseases and AIDS in China and the Beijing Institute of Biological Products. It consists of two components: the HIV-1 DNA vaccine and the recombinant vaccinia virus (rTV) AIDS vaccine. In accordance with NMPA requirements, the Phase I clinical trial protocol is designed to proceed in a stepwise manner, divided into two stages: Ia and Ib.

The Ia trial will observe the safety and immunogenicity of the rTV vaccine administered alone in 12 subjects. Following the acute reaction observation period after the Ia phase vaccination, safety data will be summarized and reported to the NMPA, and the Ib phase trial will commence upon receiving NMPA approval. A total of 48 subjects will be required for the trial, with an expected total study duration of approximately 58 weeks.

The Ia trial requires 12 subjects, including those who have and have not been vaccinated against smallpox, with a study duration of 26 weeks. The primary objective is to observe the safety and tolerability of administering either one or two doses of the rTV vaccine via bifurcated needle in healthy volunteers who have previously received or not received the smallpox vaccine, and to preliminarily assess its immunogenicity. Based on the occurrence of reactions to the rTV vaccine vector—the Tian Tan strain of vaccinia virus—the Ia phase trial will be divided into two stages: the acute reaction observation phase (weeks 0-8 of the trial) and the recovery phase observation (weeks 9-26 of the trial). The acute reaction observation phase will monitor typical post-vaccination reactions and any local or systemic adverse reactions occurring within 3-5 weeks thereafter. Upon completion of this phase, the trial will proceed to the recovery phase, where safety and immunogenicity will be observed, including the detection of immune responses specific to HIV antigens in the subjects, while continuing to monitor the various indicators from the first phase.

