### 6.4.3 Determination of Success of rTV Vaccination and re-Vaccination

This trial uses the historical response to the Tian Tan strain vaccinia virus as a reference for the expected response following rTV vaccination.

Based on smallpox vaccination experience, first-time vaccine recipients typically exhibit a progression of skin reactions at the vaccination site, including papules, vesicles, pustules, scabs, and scab shedding, which generally takes about 3 weeks (see Appendix 6 for details). In individuals revaccinated with vaccinia virus, successful vaccination also follows this progression but with milder reactions and a shorter duration. For the rTV vaccine, the insertion of the HIV gene has significantly reduced the virulence of the Tian Tan strain vaccinia virus, and animal studies have shown that the toxicity of the rTV vaccine is 100–1000 times lower than that of the Tian Tan strain vaccinia virus. Therefore, the skin reaction induced by the rTV vaccine in humans may be milder than that of the Tian Tan strain smallpox vaccine. Additionally, due to technical issues, the vaccination site may only show mild needle trauma without the typical pustule formation, indicating vaccination failure.

For these reasons, rTV vaccination is considered unsuccessful if both of the following conditions are met:

1. The vaccination site shows no pustule formation as described above;
2. Serum vaccinia antibodies do not seroconvert (for individuals initially negative for vaccinia antibodies) or show no increase in antibody titer compared to pre-vaccination levels (for individuals initially positive for vaccinia antibodies) two weeks after vaccination.

In the Phase Ib trial, the data management center will unblind the clinical observers (while laboratory personnel remain blinded) on the third day after rTV vaccination to determine whether the rTV vaccination was successful. For individuals with unsuccessful rTV vaccination, a re-administration of the same dose will be performed on the contralateral upper arm four weeks after the first vaccination. Follow-up procedures after re-administration will follow the same protocol as after the initial rTV vaccination.

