## 6.7.2 Early Termination of the Clinical Study

In the low-dose combined immunization group, if three or more vaccine-related adverse events of grade  $\geq 3$  (excluding fever above 39°C for no more than 3 days) occur after each vaccination, the sponsor and the clinical trial unit should terminate subsequent vaccinations for all groups. However, follow-up for the affected participants should continue at least until the adverse events are resolved.

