|                    | Generalized Rash                             | Scattered maculopapular rash (<5 areas), no itching or other symptoms | Scattered macules or papules (>5 areas), itching or other symptoms, no treatment required | Diffuse macules or papules, or exudative rash, requires medication   | Rash involving mucous membranes, exfoliative dermatitis, or erythema multiforme, or Stevens-Johnson syndrome |
| rTV vaccine | Injection Site
Papules                    | Diameter 1.1–1.5 cm                                                   | Diameter 1.6–3 cm                                                                         | Diameter >3 cm                                                       |                                                                                                              |
|                    | Injection Site or
Swelling
Redness     | Diameter 3–5 cm                                                       | Diameter 5.1–10 cm, improves within 5 days                                                | Diameter 5.1–10 cm, persists for over 5 days, or diameter >10 cm     |                                                                                                              |
|                    | Injection Site
Induration                 | Diameter 1.1–1.5 cm                                                   | Diameter 1.6–3 cm                                                                         | Diameter >3 cm                                                       |                                                                                                              |
|                    | Injection Site
Blisters                   | Diameter 1.1–1.5 cm                                                   | Diameter 1.6–3 cm                                                                         | Diameter >3 cm                                                       |                                                                                                              |
|                    | Injection Site
Pustules                   | Diameter 1.1–1.5 cm                                                   | Diameter 1.6–3 cm                                                                         | Diameter >3 cm                                                       | Pustules continue to expand without scabbing after 2 weeks; gangrene or exfoliative dermatitis               |

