### I. General reactions after vaccination

#### (I) Typical local reactions after vaccination

After the successful smallpox vaccination, there are generally papules, blisters, pustules, crusting and scab falling off at the injection site, and also small lesions papules and blisters (called sub-pox) can be seen around the damaged skin, accompanied by localized itching and pain.

Typical local reactions after smallpox vaccination occur at the following time:

| Time After accination | Typical Vaccination Reaction                                                                                                         |
|-----------------------|--------------------------------------------------------------------------------------------------------------------------------------|
| Day 3-4               | A papule appears at the vaccination site.                                                                                            |
| Day 5-6               | The papule develops into a vesicle (blister) with a surrounding red halo, and the top of the vesicle becomes umbilicated (indented). |
| Day 8-9               | The vesicle turns into a pustule, reaching its maximum size between days 8 and 10.                                                   |
| Day 12+               | The pustule gradually dries and scabs begin to form.                                                                                 |
| Day 17-21             | The scab falls off, leaving a permanent scar.                                                                                        |

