## **(II) Common systemic signs and symptoms after vaccination**

Systemic symptoms after smallpox vaccination and their occurrence rates are: fever (30%), headache (40%), myalgia (20%), nausea (20%), fatigue (50%) and regional lymph node enlargement (50 %). These signs and symptoms usually go away within 2 weeks after vaccination by themselves or by only symptomatic treatment.

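### At the rTV step the section 6.7.2 stopping rule has no observation window, and Table 5 leaves about two weeks for low-dose events to be found, graded and confirmed before high-dose rTV is given

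*Protocol*

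**What the plan says.** Section 6.7.2 covers the low-dose combined immunization group. If three or more related events of Grade 3 or higher (short high fever excepted) are counted after each vaccination, "the sponsor and the clinical trial unit should terminate subsequent vaccinations for all groups". Every vaccination is covered, so rTV is included. No period of observation is attached.

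Table 5 in section 6.4.2 gives rTV to the low-dose group (12 people) in the week 12 column. It gives rTV to the high-dose group (12 people) and rTV placebo to the DNA-only group (6 people) in the week 14 column.

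The text of section 6.4.2 sets a safety assessment within two weeks of each DNA dose in the low-dose subgroup. It sets none after rTV. Its condition for proceeding to rTV refers to events after the third DNA dose. The diary runs 2 weeks after DNA and 4 weeks after rTV. Visits after rTV fall on day 3 and at weeks 1, 2, 4 and later.

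On the expected course, section 6.4.3 describes a sequence from papule to scab shedding in first-time recipients, "which generally takes about 3 weeks". In people vaccinated before, "successful vaccination also follows this progression but with milder reactions and a shorter duration". Annex 6 has the pustule "reaching its maximum size between days 8 and 10" and the scab falling off on days 17 to 21. Of the common systemic reactions it says: "These signs and symptoms usually go away within 2 weeks after vaccination by themselves". One Grade 4 alternative for rTV pustules in Annex 2 reads "Pustules continue to expand without scabbing after 2 weeks".

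**The concern.** For DNA, three timings agree: a 2-week review, a 2-week diary and a 2-week offset between the dose levels. For rTV the diary doubles to 4 weeks, the expected local course is about 3 weeks and no review period is set, yet the offset stays at 2 weeks.

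The rTV go-ahead does not look at low-dose rTV events. That leaves section 6.7.2 as the only stated rule by which such events would stop high-dose rTV, and the timetable was not drawn to serve it. Followed as written, up to 12 high-dose participants can receive a replicating vector before the low-dose count that should stop them is complete, graded and confirmed. Section 4 describes this as the first human trial of the DNA and vaccinia combination.

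**Working it through.** **1. The offset.** Table 5: 14 − 12 = 2 weeks = 14 days. The earlier steps have the same offset: 2 − 0, 6 − 4 and 10 − 8 weeks.

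**2. What the rule can still stop after low-dose rTV.** The week-14 vaccinations, 12 + 6 = 18 people, and any rTV re-administrations. Section 6.4.3 puts re-administration four weeks after the first rTV, so from week 12 + 4 = 16 in the low-dose group and 14 + 4 = 18 in the high-dose group.

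**3. Offset against the protocol's own periods.**

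| | DNA | rTV |
|---|---|---|
| Offset, low to high dose | 14 days | 14 days |
| Diary | 14 days | 28 days |
| Stated review period | 2 weeks | none |
| Stated local course | – | about 21 days |

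For rTV, 14/28 = 50% of the diary period and 14/21 = 67% of the local course have passed when high-dose rTV is due.

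**4. What falls inside 14 days.** The pustule peak on days 8 to 10 comes 14 − 10 = 4 to 14 − 8 = 6 days before high-dose rTV. In the rTV block of Annex 2, Grade 3 for papules, induration, blisters and pustules depends on diameter alone, and redness or swelling above 10 cm qualifies at once. Common systemic reactions have usually gone by two weeks. The day 3 and week 1 visits have taken place.

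**5. What can fall outside.**
- The Grade 4 alternative for pustules still expanding after 2 weeks cannot be met by day 14.
- Redness of 5.1 to 10 cm becomes Grade 3 only after persisting for more than 5 days, so it may be graded late, depending on onset.
- The week-2 visit falls in the week of high-dose rTV (12 + 2 = 14).
- Relatedness becomes final only after discussion between sponsor and site and written confirmation, with no time limit (section 6.5.6). Grade 3 reports may take 2 working days after the decision (section 6.5.7).
- The monitoring board meets every two months (section 7.3.1).

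**6. Illustration of the loss.** Let p be the chance that a low-dose participant has a related Grade 3 or higher event after rTV, and f the share of such events known and confirmed before high-dose rTV. The documents give neither, so both are assumptions. The rule counts events; the model allows at most one per participant. The chance that the rule trips in time is P(X ≥ 3) with X ~ Binomial(12, p·f).

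Example, p = 0.2 and f = 2/3, so p·f = 0.1333:
1 − [0.8667^12 + 12(0.1333)(0.8667^11) + 66(0.1333²)(0.8667^10)] = 1 − [0.180 + 0.332 + 0.280] = 0.208.

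| p | no time limit | f = 0.9 | f = 2/3 | f = 0.5 |
|---|---|---|---|---|
| 0.1 | 0.111 | 0.087 | 0.041 | 0.020 |
| 0.2 | 0.442 | 0.370 | 0.208 | 0.111 |
| 0.3 | 0.747 | 0.669 | 0.442 | 0.264 |
| 0.5 | 0.981 | 0.958 | 0.819 | 0.609 |

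**7. What Phase Ia adds.** No related Grade 3 or higher event in 12 people: the one-sided 95% upper bound is 1 − 0.05^(1/12) = 0.221. This is for rTV without DNA priming, with one- and two-dose recipients pooled.

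**The case against.** The strongest reply is that the rule works well enough at this step. Severity of the local reaction is mostly known by day 10, most Grade 3 criteria need only a diameter, and common systemic symptoms have usually gone within two weeks. The three weeks run to scab shedding, not to the point at which severity is known. The course is shorter in previously vaccinated people, who are meant to be half of each dose subgroup. Both dose groups receive the same rTV dose, chosen after Phase Ia showed no related Grade 3 or higher event in 12 people, so only the DNA background differs. The board can recommend termination at any meeting. Section 6.7.2 does not say that it is meant to hold high-dose rTV until low-dose follow-up is complete.

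Most of this stands, and it limits the point. A reader might infer that the rule can hardly act at the rTV step; the timings in Annex 6 and the criteria in Annex 2 do not support that. A reader might also subtract 14 days from the 3-week course, or from the Synopsis text on "any local or systemic adverse reactions occurring within 3-5 weeks thereafter", and report a 7- to 21-day shortfall. That sets scab shedding and a Phase Ia monitoring period against time to detection, which are different things. The day 8 to 10 peak belongs to the pustule and cannot be used to date redness.

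The rare late reactions in Annex 6 add little. Encephalitis appears on days 9 to 15, mostly inside the gap. The group of abnormal reactions that includes it is put at about 5.6 per million, 80% in infants and immunocompromised people. Such events would not yield three counts among 12 participants.

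The reply does not supply the missing window. Once low-dose rTV has been given, the week-14 vaccinations are the only scheduled ones left for the rule to stop, and nothing says what must be known before they go ahead.

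**Conclusion.** The point holds as a weakness of timing and wording. Section 6.7.2 applies to rTV without an observation window, and Table 5 nominally lets high-dose rTV begin 14 days after low-dose rTV. The rule can then act for the high-dose arm only on events detected, graded and confirmed as related within about two weeks. Up to 12 rTV recipients are concerned; the 6 placebo recipients share the timetable.

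The size of the loss depends on how many events are confirmed late, which the documents do not allow one to estimate. In the illustration it is small if 90% are known in time (0.747 to 0.669 at p = 0.3) and substantial if two-thirds are (0.442 to 0.208 at p = 0.2). These figures show direction and range and are not estimates.

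The 14 days is also nominal. Enrolment is sequential, and the protocol does not say which low-dose participant anchors the offset. Later low-dose vaccinations shorten individual gaps and later high-dose enrolment lengthens them. It would go too far to call 14 days the most favourable case, or to say that all 12 are certainly affected.

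**What to change.** The sponsor, investigator and monitoring board should reconcile section 6.4.2, Table 5, section 6.4.3 and section 6.7.2. The protocol should state:
- which low-dose rTV safety information must be collected, graded and confirmed as to relatedness, and reviewed, before the first high-dose rTV vaccination;
- the period after rTV over which section 6.7.2 counts events;
- which low-dose participant's vaccination date anchors the Table 5 offset.

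The timetable should then deliver that information. The interval and the criteria are for the sponsor, investigator and board to set; none is proposed here.

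The cost is protocol wording. If the offset changes, the second phase may take a few more weeks of calendar time. No extra participants are needed.

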## 6.8 HIV-positive Problems and Treatment in the Study

### 6.8.1 Positive HIV Antibody Caused by Vaccination

Participants may test positive for HIV antibodies after vaccination. Upon the participant's request, the National Center for AIDS/STD Control and Prevention (NCAIDS) will conduct additional nucleic acid testing to distinguish between HIV infection and HIV antibody positivity caused by vaccination. For participants who test positive on ELISA due to vaccination, NCAIDS will invite them annually for HIV antibody testing until the antibodies turn negative.

To mitigate potential social discrimination in areas such as education, employment, healthcare, and international travel, NCAIDS will issue a participation certificate card to participants, confirming their involvement in the AIDS vaccine clinical trial. The card will include the contact information of the relevant responsible person from the sponsor and bear the official seal of the National Center for AIDS/STD Control and Prevention, China CDC,

for use by participants as needed.

### **6.8.2 HIV Infections during the Study**

If a participant tests positive for HIV antibodies or nucleic acids during the trial due to reasons unrelated to vaccination, the following steps will be taken:

1. Discontinue the participant's immunization:
  - Stop all further vaccinations for the participant.
2. Refer the participant to a medical institution:
  - Based on the participant's wish, recommend them to seek medical care at a healthcare facility.
3. Provide counseling by clinical trial unit researchers:
  - Offer guidance on the following issues:
    - Psychological and social aspects of HIV infection;
    - Partner-related concerns;
    - Measures to avoid infecting others.
4. Conduct immunological follow-up for participants who acquire HIV during the trial:
  - The content and frequency of follow-up will be determined by the clinical researchers and the sponsor, based on the number of vaccinations received and the progression of the disease (including viral load and CD4 count).

## **6.9 Data Management**

The data management for this study is the responsibility of the Health Statistics Office of the Chinese Center for Disease Control and Prevention (CDC).

### **6.9.1 Data Management System**

The data management system used in this study is DataFax 3.7, a specialized system for managing clinical trial data.

The DataFax system is a computerized data management system that includes data transmission, database creation, data entry, data quality control, and data reporting. Its primary working principle involves transmitting scanned images of survey forms from the research site to the data center via fax or the internet. The DataFax system at the data center uses Intelligent Character Recognition (ICR) to convert these images into data, which is then entered into the study project database. All faxed images are stored on disks.

The DataFax system audits the data through pre-set quality control procedures and generates quality reports highlighting any issues. These reports are sent back to the clinical research site via fax or the internet. Clinical researchers can then immediately verify, correct, and resolve the identified issues, providing timely feedback to the data center.

Below is a schematic diagram of the DataFax system:

[figure not shown]

**Figure 2. Schematic Diagram of the DataFax System.**

## 6.9.2 Completion and Modification of CRF Forms

Clinical researchers complete the Case Report Forms (CRFs) for each enrolled participant. After review by data quality control personnel, the CRFs are transmitted to the DataFax system at the data center via fax or the internet.

If there are any questions or discrepancies in the CRFs, the data manager will generate a Data Resolution Query (DRQ) to inquire with the clinical researchers. The researchers should promptly address the queries, make necessary corrections on the original report forms, and then fax the updated forms back to the data center.

## 6.9.3 Lock of Database

After completing the collection of clinical and laboratory data and ensuring that the database meets the locking criteria, the clinical research unit, statistical analysts, and the sponsor will jointly lock the data. Once locked, the data files will no longer be modified. Any data errors identified after the data lock will be confirmed and corrected within the statistical analysis program.

## 6.9.4 Unblinding

In the Phase Ib trial, participants are enrolled and vaccinated with either the investigational vaccine or placebo under a blinded protocol. On days 3–4 after each rTV vaccination, once all relevant research data have been entered into the database, the blinding will be lifted jointly by the statistician, the principal investigator of the clinical trial, and the sponsor. In the event of a serious adverse event, the principal investigator of the clinical trial will perform an emergency unblinding using the emergency code-break envelope.

## 6.10 Statistical Analysis

### 6.10.1 Study Indicators

#### 1) Safety Indicators

The incidence rates of various adverse events; abnormal change rates in laboratory test results such as vital signs, physical examinations, complete blood counts, blood biochemistry, and electrocardiograms.

